### Primary Composite End Points

The primary endpoint should be a composite of cardiovascular mortality, cerebrovascular accident, nonfatal myocardial infarction, and refractory angina requiring revascularization across 5 years of follow-up.

It is expected that the need for repeat revascularization after coronary surgery with or without cardiopulmonary bypass will be similar. As mentioned, a controversy discussed in the literature indicates that coronary surgery with or without cardiopulmonary bypass circulation has equal effectiveness in terms of myocardial revascularization. Therefore, repeat interventions can be a major clinical event. Therefore repeat interventions will be considered as early failure of treatment in this study. In addition, the use of cardiopulmonary bypass can be associated with considerable cerebral injury, in particular neuropsychological deficits [11,12]. So, the primary end point in the comparison of surgery with and without cardiopulmonary bypass is also a cerebral event. This is defined as the proportion of patients free of the combined event of fatal and nonfatal cardiovascular accidents and cognitive dysfunction, whichever occurs first, to be determined in-hospital and during the 5 years of follow-up.

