**Figure 1 F1:**
[figure not shown]
**Algorithm MASS IIItrial.** Only patients eligible for off-pump can enter the study. *Crossing-over in presence of electric or hemodynamic instability.

**Table 1 T1:** Schedule of Measurements

	S	P	D	1 m	3 m	6 m	12 m	24 m	36 m	48 m	60 m
Angiograms	X		X								X
History/events	X	X	X	X	X	X	X	X	X	X	X
Anginal assessment	X	X	X	X	X	X	X	X	X	X	X
Medications	X	X	X	X	X	X	X	X	X	X	X
Physical examination	X	X	X	X	X	X	X	X	X	X	X
Electrocardiography	X	X	X	X	X	X	X	X	X	X	X
Echocardiography	X										X
Magnetic Resonance Imaging	X		X								
Neuropsychological tests	X		X		X	X					
Routine laboratory	X	X	X	X	X	X	X	X	X	X	X
ECG stress tests	X					X					X
Resource utilization	X	X	X	X		X	X	X	X	X	X
Quality of life	X					X	X	X	X	X	X
Cost-effectiveness		X	X								
Working status	X				X						

Abbreviations: S = preprocedural screening; P = procedure; D = discharge; 1 m = 1 month after intervention; 3 m to 60 m denotes months after intervention.

**Table 2 T2:** Definitions of Main Composite Primary End Points

**Cardiovascular death**	Cardiovascular mortality is included in the composite primary end point. Cardiovascular death includes fatal myocardial infarction, sudden death, untreated heart failure, fatal cerebral infarction, and hemorrhage and procedure-related fatal bleeding.

**Cerebrovascular accident**	Patients with a focal neurological deficit of central origin lasting more than 72 hours, or a focal neurological deficit of central origin lasting more than 24 hours with imaging evidence of cerebral infarction or intracerebral hemorrhage, or a nonfocal encephalopathy lasting more than 24 hours with imaging evidence of cerebral infarction or hemorrhage adequate to account for the clinical state. Retinal arterial ischemia or hemorrhage is also included. To fulfill the definitions of stroke, the deficit must be new, sudden in conset, and not attributable to any more likely alternative cause.

**Myocardial infarction**	Elevation of specific cardiac enzymes within 14 days of a revascularization procedure and presence of new Q waves in at least 2 or more contiguous leads and CK-MB elevation 5 × normal (see Appendix).

**Further revascularization**	The initial revascularization is considered completed when the patient is transferred from the operating room to bed. Refractory angina requiring revascularization was considered an end point.

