### Secondary End Points

The secondary end points in this trial include non-cardiac mortality, presence and severity of angina, quality of life using the SF-36 Questionnaire [18], and cost-effectiveness at discharge and at 5-year follow-up. In this scenario, we will analyze the cost of the initial procedure, hospital length of stay, resource utilization, repeat hospitalization, and repeat revascularization events during the follow-up. Exercise capacity will be assessed at 6-month, 12-month, and end follow-up.

In the MASS III trial, no difference is expected in cardiac outcome; nevertheless, cardiac death, myocardial infarction, and repeat revascularization procedures will be assessed in-hospital and at 1, 6, and 12 months and yearly thereafter. Cognitive function will also be assessed at baseline and at 1, 6, and 12 months. It is expected that most patients will show a decline in this early postoperative period. However, the rapid recovery and short hospital stay of the nonselected patients who undergo coronary surgery in our hospital without extracorporeal circulation suggest that the benefits of this strategy may be especially reflected in a reduction of neuropsychological injury in the early postoperative period.

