### Neurocognitive Evaluation

In evaluation of CABG patients with multivessel disease, neurocognitive status is a crucial outcome variable, along with major adverse cardiac and cerebrovascular event. A subset of subjects will be assessed using the Brain Resource Center [21] computerized neurocognitive battery. The battery is relatively short and easy to administer and score. The computerized battery measures 5 basic functions: memory, mental and psychomotor speed attention, verbal fluency, and cognitive flexibility.

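### A cerebral event is also called primary, against the single four-part composite elsewhere, and its cognitive component cannot be determined over 5 years in all patients

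*Protocol article*

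**What the plan says.** All references are to the protocol article.

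- **First primary.** Primary Composite End Points opens with: "The primary endpoint should be a composite of cardiovascular mortality, cerebrovascular accident, nonfatal myocardial infarction, and refractory angina requiring revascularization across 5 years of follow-up". The Abstract and Objectives name the same four components. Table 2, which defines the components of the primary composite, has no cognitive entry.
- **Second primary.** The same section goes on: "So, the primary end point in the comparison of surgery with and without cardiopulmonary bypass is also a cerebral event". What is counted is the share of patients without "the combined event of fatal and nonfatal cardiovascular accidents and cognitive dysfunction, whichever occurs first". The horizon covers the hospital stay and all 5 years.
- **Who is tested.** Neurocognitive Evaluation: "A subset of subjects will be assessed using the Brain Resource Center". The Abstract also limits the battery to a subset. No size is given.
- **When.** Secondary End Points: "Cognitive function will also be assessed at baseline and at 1, 6, and 12 months". In Table 1 the row "Neuropsychological tests" is marked, by column position, at screening, discharge, 3 months and 6 months.
- **Expected course.** Secondary End Points, on cognition: "It is expected that most patients will show a decline in this early postoperative period".
- **Sizing.** Methods sets one α of 0.05 and a β of 0.20. It assumes 95% freedom from cardiac event at 5 years after on-pump surgery and a decrease of no more than 10% off-pump, and requires 153 per group.

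**The concern.** A confirmatory trial has to fix which result decides it. Here one section names two different primary endpoints, the rest of the article names one, and cognition also appears under the secondary endpoints. A favourable result on either could later be presented as the primary finding.

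The cerebral endpoint also asks for something the assessments do not supply. It is a proportion of patients free of an event over 5 years, and the Statistical Analysis Plan section puts the primary analysis on the intention-to-treat principle. A patient who is never tested cannot register cognitive dysfunction, and a tested patient cannot register it after the last test. The first-event rule adds a conditional problem: if an early, passing decline counts, it settles the outcome before any lasting effect can show. Finally, an endpoint introduced as cerebral is defined through cardiovascular accidents, which read literally would bring cardiac events into it.

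**Working it through.** **1. The passages side by side**

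| Feature | Endpoint as defined | Assessment as planned |
|---|---|---|
| Status of cognition | Primary (Primary Composite End Points) | Secondary (Secondary End Points); absent from Table 2 |
| Population | Proportion of patients | Battery in a subset |
| Horizon | In hospital and 5 years | Last test at 6 months (Table 1) or 12 months (Secondary End Points) |
| Follow-up visits | First event | Discharge, 3, 6 months against 1, 6, 12 months |

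The only post-discharge month in both schedules is month 6. Clinical events are different: Table 1 records history and events at every visit to 60 months.

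**2. What the stated sample size pays for**

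Inputs from Methods: 95% on-pump, a 10% decrease read as relative (0.95 × 0.90 = 0.855), two-sided α 0.05 (sidedness assumed), power 0.80.

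n = 2 p̄(1 − p̄)(z₀.₉₇₅ + z₀.₈₀)² / d², with p̄ = (0.95 + 0.855)/2 = 0.9025 and d = 0.095:

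n = 2 × 0.9025 × 0.0975 × 7.849 / 0.009025 = 153.05.

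The form with separate null and alternative variances gives 152, and its power at 153 per group is 0.80. If the 10% is read as absolute (95% vs 85%), Fisher's exact test at 153 per group has power 0.807. Either way the number is reached with the full 0.05 on the cardiac endpoint.

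**3. Error rate if either endpoint could win at 0.05 (assumption)**

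1 − 0.95² = 0.0975 under independence. The upper bound is 0.05 + 0.05 = 0.10. With correlated test statistics it is 0.095, 0.091 and 0.078 at correlations 0.3, 0.5 and 0.8. An illustrative equal split (0.025 each) would lower cardiac power at 153 per group from 0.80 to 0.71, and 185 per group would be needed to restore 0.80.

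**4. Power for the cognitive component**

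The Rationale cites cognitive deficit in up to 38%. The comparison rate of 25%, the tested fraction f and two-sided α 0.05 are assumptions.

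Power = Φ[(d − 1.96·√(2p̄(1 − p̄)/n)) / √((p₁(1 − p₁) + p₂(1 − p₂))/n)].

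*Tested only* uses n = 153f with rates 38% and 25%. *Untested as event-free* uses n = 153 with rates 38%·f and 25%·f.

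| Fraction tested | n tested per group | Tested only | Untested as event-free |
|---|---|---|---|
| 1/4 | 38 | 23% | 18% |
| 1/3 | 51 | 29% | 23% |
| 1/2 | 76 to 77 | 41% | 34% |
| 3/4 | 115 | 56% | 52% |
| all | 153 | 69% | 69% |

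(With the one-third rates first rounded to 12.7% and 8.3%, the 23% in the last column becomes 24%.)

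The assumed effect matters as much. For 80% power with everyone counted tested, 38% vs 28% needs 346 per group, 38% vs 25% needs 200, and 38% vs 19% needs 88.

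**The case against.** The strongest reply is that this is a condensed article. A multiplicity rule, the subset size and a threshold for cognitive dysfunction may stand in a fuller document. That is fair for those details, and their absence is not the point here. It does not answer the conflict, because the definitions that are published contradict each other.

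The reply does rule out several stronger readings that a reader might infer:

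- **The error rate is inflated to 9.75%.** Nothing says that each endpoint is tested at 0.05 or that either suffices. If both had to succeed, there would be no inflation.
- **The whole cerebral endpoint is confined to a subset and to the first year.** Only its cognitive component is. Clinical events are followed to 60 months with no subset restriction. The subset is stated for the computerized battery; the Table 1 row and Secondary End Points do not repeat it. The battery is the only cognitive instrument described, so the subset reading is the natural one, but the gap between 12 months and 5 years does not depend on it.
- **Most patients will have the event.** The article expects a decline in most patients. It gives no threshold that equates decline with dysfunction, and its own cited figure is up to 38%.
- **A later stroke is lost.** It would be lost to the cerebral first-event endpoint, but it still counts in the four-part composite.
- **Counting untested patients as event-free cuts power from 69% to 23%.** No such rule is stated. If a third are tested, the step from 69% to 29% comes from subset size alone; the counting rule accounts only for 29% to 23%.

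The mention of cardiovascular accidents is probably a slip of wording, and minor by itself.

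**Conclusion.** The point holds as a contradiction in the text. The article names one primary endpoint in the Abstract, Objectives and Table 2, two in Primary Composite End Points, and places cognition among the secondary endpoints. The cognitive component of the second primary cannot be determined as defined, since testing ends at 6 or 12 months against a 5-year horizon, on two schedules that disagree, with the battery given to a subset. This part needs no assumption beyond reading Table 1 by column position.

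The numbers are conditional. The stated sample size spends the whole 0.05 on the cardiac endpoint, so none of the stated α is left for a second primary; family-wise error of up to about 10% follows only if either could win at 0.05. The power of 23% to 56% in tested patients rests on the assumed 38% vs 25% and on testing a quarter to three quarters. Dominance by transient early results follows only if early decline counts as dysfunction.

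**What to change.** 1. Keep the four-part composite as the only primary endpoint and remove the statement that a cerebral event is also primary.
2. Make stroke (fatal and nonfatal, all patients, 5 years) and cognition two separate secondary endpoints.
3. Analyse cognition in tested patients only, as change from baseline at one named visit. Month 6 is the natural choice, being the only follow-up month in both schedules.
4. Reconcile Table 1 with Secondary End Points on the cognitive visits.
5. Reconcile the term cardiovascular accidents with the label cerebral event; cerebrovascular may be meant.

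The cost is wording in the protocol and analysis plan, with no change to sample size. Cognition can no longer be claimed as a primary result. The subset analysis may have low power (29% under the assumed rates if a third are tested), and the plan should say so rather than let a null result be read as no difference.

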### Secondary End Points

The secondary end points in this trial include non-cardiac mortality, presence and severity of angina, quality of life using the SF-36 Questionnaire [18], and cost-effectiveness at discharge and at 5-year follow-up. In this scenario, we will analyze the cost of the initial procedure, hospital length of stay, resource utilization, repeat hospitalization, and repeat revascularization events during the follow-up. Exercise capacity will be assessed at 6-month, 12-month, and end follow-up.

In the MASS III trial, no difference is expected in cardiac outcome; nevertheless, cardiac death, myocardial infarction, and repeat revascularization procedures will be assessed in-hospital and at 1, 6, and 12 months and yearly thereafter. Cognitive function will also be assessed at baseline and at 1, 6, and 12 months. It is expected that most patients will show a decline in this early postoperative period. However, the rapid recovery and short hospital stay of the nonselected patients who undergo coronary surgery in our hospital without extracorporeal circulation suggest that the benefits of this strategy may be especially reflected in a reduction of neuropsychological injury in the early postoperative period.

### Patients

Patients with angiographically documented proximal multivessel coronary stenosis of more than 70% by visual assessment, stable angina, and preserved ventricular function were considered for inclusion in this study. Furthermore, they were eligible if they were referred for isolated coronary bypass surgery for the first time and the off-pump procedure was deemed technically feasible. Patients were enrolled and randomized if surgeons agreed that revascularization could be attained by either strategy. This selection predominantly depends on the precise location of the stenoses, the anticipated capacity of the heart to endure temporary occlusion of the involved coronary arteries, and hemodynamic consequences of local immobilization of the ventricular wall. In these conditions, bypass grafting of posterior coronary arteries may result in a significant drop in left ventricular stroke volume upon presentation of these vessels [19].

All angiograms were reviewed and a surgical plan was documented before randomization. The selection criteria for the MASS III trial are depicted in Table 3.

**Table 3 T3:** Eligibly criteria.

INCLUSION CRITERIA

Male or female age 18 years or older.
Patients with stable angina pectoris and/or documented ischemia due to multivessel disease and preserved ventricular function.
Angiographically confirmed multivessel CAD lesions with ≥70% in at least 2 major epicardial vessels and at least 2 separate coronary artery territories: LAD, LCX, and RCA.
Patients who are eligible for coronary surgery both with and without cardiopulmonary bypass circuit.
Nonsignificant left main stenoses can be included.
Willing to comply with all follow-up study visits.
Signed and received a copy of the informed consent.

EXCLUSION CRITERIA

Age under 18 years
Severe congestive hearth failure NYHA Class III or IV or pulmonary edema.
Prior valve replacement or CABG coronary surgery.
Prior PCI with stent implantation within 6 months.
Prior stroke within 6 months or patients with stroke at more than 6 months with significant residual neurological involvement, as reflected in a Rankin score > 1.
Need for concomitant major surgery, eg, valve replacement, resection ventricular aneurysm, congenital heart disease vascular surgery of the carotid artery, or thoracic-abdominal aorta.
Concomitant medical disorders making clinical follow-up at least 5 years unlikely or impossible, eg, neoplasic, hepatic, or other severe disease.
Q-wave myocardial infarction in the previous 6 weeks.
Hemorrhagic diathesis or hypercoagulability.
Thoracic deformations technically precluding surgery without extracorporeal circulation.
Unable to give informed consent.

### Surgical Technique

#### General

Trial operators were required to perform optimum coronary revascularization in accordance with current best practices. The surgery was performed by physicians experienced in both on-pump and off-pump bypass surgery. Surgical access to the heart was through a standard median sternotomy in all cases. All incisions and closure techniques were the same for groups, limiting variability and maintaining blinding of group assignment for patients, family, and referring cardiologists. A cell saver reservoir (COBE Cardiovascular, Inc. Arvada, CO) was spun down and returned to all patients when the quantity was sufficient.

#### Off-pump strategies

Off-pump surgery used the Octopus stabilizer described in detail elsewhere [14]. In brief, the distal ends of the 2 suction arms of the stabilizer are placed on the beating heart on both sides of the target coronary artery. The proximal parts are fixed to the operating table. Through the application of negative pressure, the target area of the heart is sufficiently immobilized to allow the safe construction of the anastomosis of the graft with the recipient artery.

#### On-pump technique

Conventional coronary artery surgery with cardiopulmonary bypass was accomplished with every effort made to minimize the impact of cardiopulmonary bypass. Patients without diabetes received 1 gram of hydrocortisone sodium succinate (SoluCortef, Pharmacia & Upjohn Co., New York, NY) intravenously before of anesthesia. This procedure will be made only in the on-pump technique. The patients were routinely cooled to 34° for operations with 3 grafts and 32° for 4 grafts or more. Cold-blood cardioplegia was accomplished with anterograde delivery through the aortic root and retrograde delivery through the coronary sinus. A heparinization protocol of 300 U per kilogram for on-pump surgery and half-dose heparin for off-pump surgery was followed. Protamine was used to reverse the effects of heparinization only in the on-pump patients. All anastomoses were sutured by hand. In the off-pump patients, intracoronary shunts were not used routinely; indications for use included poor visibility, ST-segment changes, and homodynamic instability.

### Quality of Life and Cost-effectiveness

Health-related quality of life and treatment costs will be assessed to evaluate the relative cost-effectiveness for the MASS III trial population. Heath-related quality of life and functional status will be assessed using a combination of generic and disease-specific measures selected to cover a broad range of potential health domains that may be affected by coronary artery disease, its treatments, and complications. The SF-36 Questionnaire will be used to assess patients' utilities [18]. Utilities are a global rating of health that reflects a patient's preference for his current health status relative to perfect health and are particularly important outcome measures for cost-effectiveness analysis [20]. Medical care resource utilization and cost data will be collected prospectively for the index hospitalization up to discharge and 5-year follow-up for all patients including all costs associated with the index procedure. For each index revascularization procedure, detailed resource utilization will be collected using a standardized case report form. Follow-up medical resource utilization (including hospitalization, out-patient services, and cardiovascular medications) will be assessed by detailed questionnaires that will be completed during each scheduled patient contact.

### Neurocognitive Evaluation

In evaluation of CABG patients with multivessel disease, neurocognitive status is a crucial outcome variable, along with major adverse cardiac and cerebrovascular event. A subset of subjects will be assessed using the Brain Resource Center [21] computerized neurocognitive battery. The battery is relatively short and easy to administer and score. The computerized battery measures 5 basic functions: memory, mental and psychomotor speed attention, verbal fluency, and cognitive flexibility.

### Statistical Analysis Plan

Patients eligible for the MASS III trial are invited to the outpatient clinic to receive additional information. Candidates for the trial admitted to a referral hospital are visited by one of the trial monitors. After giving consent, patients are randomized. To ensure a reasonable balance, assignment is performed according to a computer-generated list of random permuted blocks that are unknown by the investigators. After randomization, patients are scheduled for the allotted treatment.

The goal of the main analysis is to compare the primary outcome events in this trial. Kaplan Meyer curves will be used for graphic comparison. All values are expressed as mean ± standard deviation or percentage. The continuous variables are compared by the Wilcox rank sum test, whereas the discrete variables are analyzed with Fisher's exact test. The occurrence of outcome events will be compared by means of Cox's proportional hazards model yielding a hazard ratio. The primary data analysis will be based on the intention-to-treat principle. Interim analyses will be carried out annually to evaluate the safety.

For both treatment strategies, the cost of diagnostic procedures, treatment procedures, complications, and short- and long-term differences in effects will be estimated. Marginal costs in monetary terms will be calculated by multiplying unit costs and marginal medical consumption as recorded for each patient.

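### The only test named for continuous variables is an unadjusted rank-sum test, which makes no efficient use of the screening values and gives no estimate on the scale reported

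*Protocol article*

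**What the plan says.** The Statistical Analysis Plan section gives a reporting rule, "All values are expressed as mean ± standard deviation or percentage", and then a single test: "The continuous variables are compared by the Wilcox rank sum test". Discrete variables go to Fisher's exact test and outcome events to a Cox model. No baseline covariate, change score or repeated-measures model is mentioned for continuous data.

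The endpoints that this rule would reach are under Secondary End Points:
- Quality of life and cost: "quality of life using the SF-36 Questionnaire [18], and cost-effectiveness at discharge and at 5-year follow-up".
- Exercise: "Exercise capacity will be assessed at 6-month, 12-month, and end follow-up".
- Cognition: "Cognitive function will also be assessed at baseline and at 1, 6, and 12 months". Under Neurocognitive Evaluation this is limited: "A subset of subjects will be assessed using the Brain Resource Center".

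Baseline values exist for three of these. In Table 1 the rows for "Quality of life", neuropsychological tests and ECG stress tests are all marked in the screening column. Quality of life is then marked at six later visits (6, 12, 24, 36, 48 and 60 months). The follow-up times for cognition and exercise differ between Table 1 and the text. That is a separate matter, since a screening value is scheduled for both in Table 1.

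**The concern.** A patient's score before surgery usually predicts the score afterwards. A two-sample rank-sum test on follow-up values ignores that information and carries the between-patient spread into the comparison as noise. The test also yields a p-value rather than an effect size. Readers would see means and SDs by arm, next to a p-value that does not test the difference in those means and has no interval for it.

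At stake is precision on quality of life, cognition and exercise. This matters to the trial's own argument: Secondary End Points expects no difference in cardiac outcome and suggests that the benefit of off-pump surgery may show especially as less early neuropsychological injury.

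**Working it through.** **The plan's own figure.** No sample size or power is stated for a continuous endpoint. The only figure is 153 per group for the primary composite (Methods). Reading the 10% decrease as relative (95% to 85.5%), with two-sided 0.05 and 80% power:

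n = [1.96·√(2·0.9025·0.0975) + 0.8416·√(0.95·0.05 + 0.855·0.145)]² / 0.095² = (0.822 + 0.349)² / 0.009025 ≈ 152.

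That is close to 153. It serves here only as the number per arm.

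**Inputs.** n = 153 per arm (Methods); two-sided 0.05 (alpha from Methods, sidedness assumed). Assumptions not in the document: outcome SD 1, roughly normal; effect 0.3 SD; baseline-to-follow-up correlation r of 0.3, 0.5 or 0.7.

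**Formula.** Power = Φ(0.3 / SE − 1.96), with SE = s·√(2/153) = 0.1143·s.
- Rank-sum on follow-up values: s = √(π/3) = 1.023 (its large-sample efficiency under normality).
- ANCOVA: s = √(1 − r²).

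| Method | s | SE | Power |
|---|---|---|---|
| Rank-sum, any r | 1.023 | 0.1170 | Φ(0.604) = 72.7% |
| ANCOVA, r = 0.3 | 0.954 | 0.1091 | Φ(0.791) = 78.5% |
| ANCOVA, r = 0.5 | 0.866 | 0.0990 | Φ(1.070) = 85.8% |
| ANCOVA, r = 0.7 | 0.714 | 0.0816 | Φ(1.714) = 95.7% |

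Simulation at the same size agrees: rank-sum 73%; ANCOVA 78%, 85% and 95%.

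**Detectable difference at 80% power**, (1.96 + 0.8416)·SE: rank-sum 0.328 SD; ANCOVA 0.306, 0.277 and 0.229 SD at r = 0.3, 0.5 and 0.7.

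**If change from baseline is what gets ranked.** Then s = √(2(1 − r)·π/3), and power is 58%, 73% and 91%. That is below ANCOVA at each r, and at r = 0.3 it is worse than ranking follow-up values.

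**Skewed outcome.** Assume lognormal baseline and follow-up, log-SD 1, and a shift of 0.3 on the log scale (4,000 simulated trials per setting).
- Rank-sum: about 72%.
- ANCOVA on the raw scale: about 54% to 57% (two separate simulations), 61% and 73% at latent correlations of 0.3, 0.5 and 0.7. It is worse than rank-sum at the first two and level at the third.
- ANCOVA on logs: the normal table above applies unchanged.
- ANCOVA on ranks (same simulation; ranks do not change under the log transform): about 76%, 83% and 94%.

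The gain therefore comes from adjusting for baseline on a suitable scale, not from replacing ranks with raw means.

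**The case against.** The strongest reply is that the rank-sum sentence is generic. It stands beside a reporting convention and is never tied to SF-36, cognition or exercise, and a condensed article may leave model details to a fuller plan. It is true that the sentence names no endpoint. But the article does name a test, and it offers no other method that would cover these variables, so the point concerns a stated choice rather than a missing detail.

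Several stronger readings are tempting, and the document does not support them:

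- **That the analysis is invalid.** It is not. Under randomisation the rank-sum test remains a valid test of equal distributions.
- **That baseline is certainly discarded.** The article does not say whether follow-up values or changes are ranked. With changes, baseline is used, but less efficiently than in ANCOVA, as the working shows.
- **That costs will be compared by ranks.** Costs have their own paragraph, which plans estimation: "Marginal costs in monetary terms will be calculated by multiplying unit costs and marginal medical consumption as recorded for each patient". No rank test is assigned to them. The lack of an interval for mean cost is something a condensed article may leave to the full plan. Only if the rank-sum sentence is meant to include costs would it miss its target, because cost-effectiveness rests on arithmetic means.
- **That cognition suffers most because few patients are tested.** The size of the subset is not given. Cognitive dysfunction also enters an event-free proportion under Primary Composite End Points, where the rank-sum test has no role.
- **That the gain equals a fixed multiple of the sample size.** The factor 1 − r² compares ANCOVA with an unadjusted comparison of means under near-normality, not with a rank-sum test in general.

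It also stands that exercise capacity is never defined as a continuous measure. The point reaches it only if it is one.

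**Conclusion.** The concern holds as a loss of precision, and a mismatch between test and reporting scale, on secondary endpoints. With 153 per arm, a near-normal outcome and an assumed 0.3 SD effect, power rises from about 73% to about 78%, 86% or 95% at correlations of 0.3, 0.5 or 0.7. The effect size, the correlations and the normality are all assumptions. With strong skew and no transformation the advantage can vanish or reverse. No error-rate problem is shown, and the primary time-to-event comparison is unaffected. This is an improvement that should be made; it does not undermine the trial.

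**What to change.** Replace the rank-sum sentence, before outcomes are analysed, with wording to this effect:

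1. SF-36 scores, continuous cognitive scores and any continuous exercise measure are compared by ANCOVA, or by a repeated-measures model where there are several follow-up visits, with treatment and the screening value as covariate.
2. Markedly skewed outcomes are transformed, or analysed by the same model on ranks.
3. The adjusted treatment difference is reported with its 95% CI.
4. The rank-sum test is kept as a sensitivity analysis, stating whether follow-up values or changes are ranked.
5. If the rank-sum sentence was meant to cover per-patient costs, they are exempted, and the difference in arithmetic means is reported with a bootstrap interval.

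The cost is a change of wording and a little programming. All the screening values are already scheduled, so no new data, visits or patients are needed.
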